### 7.6.2 Safety Assessments

All subjects will have a physical examination at screening.

Routine blood tests: Serum-creatinine, urea, glomerular filtration rate (MDRD), blood count (haemoglobin, leukocytes, platelets), aspartate aminotransferase, alanin aminotransferase, alkaline phosphatase, and gamma glutamyl transferase will be performed at Visit 1 and Visit 4 (2-4 weeks after imaging). Adverse events will be assessed at every study visit. NCI-CTCAE v.4 will be used to report toxicity

([https://evs.nci.nih.gov/ftp1/CTCAE/CTCAE\\_4.03/CTCAE\\_4.03\\_2010-06-14\\_QuickReference\\_5x7.pdf](https://evs.nci.nih.gov/ftp1/CTCAE/CTCAE_4.03/CTCAE_4.03_2010-06-14_QuickReference_5x7.pdf))

### 7.7 Violation of eligibility criteria

If a patient has been included into the study and it turns out that he/she did not fit into the eligibility criteria, the following procedures will be followed: In case the patient has not yet been imaged, his/her participation in the trial is stopped entirely. If the patient has already undergone imaging, immediate contact with the centre for clinical study at the University of Würzburg and the coordinating investigator/the sponsor is indicated. It is mandatory to stop participating in the trial immediately in case the non-eligible patient has undergone only one imaging procedure or in case the patient has been included by error without his/her consent. In all other cases, proceed per protocol and wait for instructions. The steering committee will in each individual case discuss with the investigator whether maintenance within the FAMIAN trial is indicated. Documentation of the patient's clinical data will be continued throughout the entire trial.

## 8 BIOMETRICAL ASPECTS

The study aims to evaluate the utility of combined FDG-PET and [ $^{123}\text{I}$ ]Iodometomidate imaging for non-invasive characterization of indeterminate adrenal neoplasias. The primary objective is to demonstrate effectiveness of a test for benign adrenocortical adenomas (AA). A secondary focus is on the performance of the diagnostic AA test given ACC or non-ACC.

### 8.1 Outcome variables and measures

As this is a diagnostic study, the results of histopathology of surgical specimens as assessed by an expert pathologist will serve as the comparator (gold standard) to the results of imaging. Test performance will be assessed among participants with (sensitivity) and without (specificity) adrenocortical adenoma, as a hormonally silent adenoma does not require surgery.

#### 8.1.1 Primary variables and measures

Gold standard: An expert pathologist will classify the incidentaloma of a patient based on histopathology of surgical specimens. All removed neoplasias will be classified according to histopathological criteria. Primary classification will be all neoplasias AA or at least one neoplasmia non-AA.

Diagnostic tests: The tumors will be characterized as either positive or negative concerning FDG/Iodometomidate uptake leading to 4 different categories. The primary diagnostic test variables subsume to the indicators “all neoplasias of a patient FDG-PET negative” and “all neoplasias of a patient Iodometomidate positive”.

The diagnostic measures of primary interest are specificity, sensitivity and likelihood ratio of a positive diagnostic AA test using histopathology of the surgically removed tumor as gold standard for the differential diagnosis. Thereby the AA test uses the combined FDG-PET and Iodometomidate imaging: AA+ is defined for each neoplasmia as FDG-PET negative and Iodometomidate positive. The primary clinical outcome is the correct non-invasive diagnosis (using the combined AA test) of histologically verified adrenocortical adenoma and verified neoplasmia different from adrenocortical adenoma (for the estimation of the sensitivity and the specificity of the combined AA test).

#### 8.1.2 Secondary variables and measures

Gold standard: An expert pathologist will classify the incidentaloma of a patient based on histopathology of surgical specimens. All removed neoplasias will be classified according to histopathological criteria. Each neoplasmia will be classified as AA, ACC or another benign or malignant adrenal incidentaloma.

Usually, the gold standard diagnosis can be subsumed on a patient level. If in rare cases combinations occur, analyses may in addition be performed on a neoplasia level.

Key secondary outcome measures are the likelihood ratio of a negative diagnostic AA test a priori probabilities of AA, ACC and other benign as well as malignant adrenal incidentalomas and positive and negative predictive values.

### **8.1.3 Exploratory endpoints**

In addition, a cost effectiveness analysis will be performed comparing imaging costs with potentially avoidable costs for surgery.

Steroid profiling analysis will be used to compare the urinary steroid profile in malignant adrenal tumors with that in benign adenomas and non-adrenal lesions to assess the role of steroidobolomics for non-invasive diagnosis of adrenocortical cancer.

## **8.2 Statistical hypothesis and Confirmatory Statistical Analysis**

The confirmatory analysis consists primary of testing two hypotheses hierarchically at a two-sided type I error level of  $\alpha=5\%$ .

In a first test, for the diagnostic AA test a specificity (probability of AA- given non-AA, i.e. the / at least one patient's neoplasia is not a benign adrenocortical adenoma) of more than 90% should be demonstrated. In case of significance, in a second test it should be shown that the likelihood ratio (AA relative to non-AA) of a positive AA test (AA+) is greater than 9.

If also the second test is significant, under the accepted assumption that a priori (assessment before combined imaging and without gold standard) the probability of a benign adrenocortical adenoma (AA, all patients' neoplasias) is at least 50%, it can be statistically concluded that the positive predictive value of the diagnostic AA test (probability of a benign adrenocortical carcinoma given AA+) is greater than 90%.

An exact binomial test will be performed for testing for the first alternative hypothesis. Where required to improve efficiency, two stage designs will be specified (based on gold standard, blinded regarding diagnostic test).

Specificity and sensitivity of the AA test will be estimated with 95% confidence intervals. At least the method of Clopper and Pearson will be adopted, if possible the more efficient method of Blyth, Still and Casella will be utilized (usually in the one stage binomial test design).

The second alternative will be tested using an approximately normally distributed test statistic based on the estimators of the sensitivity and the specificity of the diagnostic AA test.

Two further statistical tests are planned in a hierarchical order at a two-sided type I error level of  $\alpha=0.05$  (confirmatory in the case of significance of the first two statistical tests, otherwise explorative):

The third test will examine the alternative hypothesis of a probability of a negative diagnostic AA test (AA-) given ACC of more than 80%.

The fourth test will examine the alternative hypothesis of a likelihood ratio (ACC relative to non-ACC) of a positive AA test (AA+) less than 7/19.

In the case of significance, under the accepted assumption that the probability of ACC is at most 12.5%, it can be statistically concluded that the probability of ACC given AA+ is less than 5%. Statistical tests and rate estimation are performed in a similar way as described before.

The analyses are conducted primarily in the spirit of the intention to treat principle (ITT), meaning that all patients with assessable endpoints will be included in the analyses regardless of violation of eligibility criteria.

### 8.3 Proposed sample size / power calculations

Sample size calculation is based on the two primary hierarchically structured two-sided level 5% tests.

For the first test, assuming an a priori probability of 60% for AA and a specificity ( $P(\text{AA-}|\text{non-AA})$ ) of 98% to be detected with a power of 80%, approximately 195 assessed patients are necessary. For the exact test, at least 70 patients with a confirmed non-AA neoplasia are necessary.

For the second test, assuming an a priori probability of 60% for AA and a specificity of 98% together with a sensitivity ( $P(\text{AA+}|\text{AA})$ ) of 92% to be detected with a power of 80%, approximately 187 assessed patients are necessary.

Thus 195 patients to be assessed are necessary. Adjusting for incomplete assessments in up to 10% of patients and a recruitment rate of 40% within screened patients, 220 patients have to be recruited and 550 to be screened.

For the third test, assuming an a priori probability of 10% for ACC (~20 ACC patients), the power to detect  $P(\text{AA-}|\text{ACC})=98\%$  is ~70%. For the fourth test, assuming a priori probabilities of 60% for AA and 10% for ACC, the power to detect  $P(\text{AA-}|\text{ACC})=98\%$  together with  $P(\text{AA+}|\text{non-ACC})=61.5\%$  is almost 80%.

The assumptions on a priori probabilities and detectable probabilities to be powered were set up in consensus at the ENSAT Cancer Imaging Study Group meeting at the 1st European Conference on Adrenal Imaging 2011.

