### 1.1 Background: Diagnostic problems in adrenal neoplasia

The management of adrenal tumors is a public health challenge of growing importance, as these tumors are detected with increasing frequency in a population that has widespread access to advanced imaging technology. The key question is, whether or not such a tumor needs to be removed by surgery. Basically this question can be divided into two separate questions:

- Is the adrenal lesion hormonally active?
- Is the tumor benign or malignant?

In non-oncological patients, adrenocortical carcinoma (ACC) is the most frequently observed adrenal malignancy with a prevalence of 4-6%. Currently, tumor size and a low lipid content of an adrenal mass and the rapidity of the wash-out of contrast medium are probably the best criteria for diagnosing ACC. Benign adrenocortical adenomas usually have a high content of lipids, resulting in a low attenuation coefficient on unenhanced CT (< 10 Hounsfield units (HU)). Furthermore, on delayed contrast-enhanced CT adenomas typically exhibit rapid wash-out of contrast medium, whereas non-adenomatous tumors display delayed wash-out of contrast material (8). However, despite these highly useful criteria, a significant number of adrenal incidentalomas (around 30% of tumors > 3 cm) are not reliably characterized

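### The stated power of about 70% for test 3 holds only if about 20 ACC patients turn up; with 195 assessed and 10% ACC, the power of the standard exact test is about 52%.

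*Protocol*

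**What the plan says.** Section 8.2 sets the level of the last two tests: "Two further statistical tests are planned in a hierarchical order at a two-sided type I error level of" 5%. They are confirmatory only if tests 1 and 2 are significant and exploratory otherwise. Test 3 asks whether the probability of a negative AA test is "given ACC of more than 80" percent. On the type of test, section 8.2 says for test 1: "An exact binomial test will be performed for testing for the first alternative hypothesis". For the later tests it says: "Statistical tests and rate estimation are performed in a similar way as described before".

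Section 8.3 then gives the power of test 3: "For the third test, assuming an a priori probability of 10% for ACC (~20 ACC patients), the power to detect" a true value of 98% is put at about 70%. Synopsis part E repeats the statement. The number to be assessed is 195, and 220 are recruited to allow for up to 10% incomplete assessments. Section 8.3 bases the sample size on tests 1 and 2 only.

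**The concern.** Test 3 is conditional on ACC histology. Nothing in the protocol fixes the number of ACC patients by quota or enrichment, so the figure of about 20 is only an expected value. Power at the expected subgroup size is often close to the average power, but not here. The smallest count at which the standard exact test can reject at all lies only about 2.5 patients below the mean.

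Test 4 comes after test 3 in the hierarchy, and with it the conclusion that the probability of ACC given a positive AA test is below 5%. A non-significant test 3 could therefore reflect too few carcinomas rather than poor performance of the imaging. A reader who takes about 70% as the chance of success would not expect that.

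**Working it through.** **Inputs.** From section 8.2: null value 80%, two-sided 5% (2.5% in the upper tail), exact binomial test. From section 8.3: true value 98%, ACC prevalence 10%, 195 assessed, 220 recruited.

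**Step 1: rejection rule.** With n ACC patients, all AA-, the upper-tail p-value is 0.8^n.
- 0.8^16 = 0.0281 > 0.025, so no outcome rejects with 16 or fewer.
- 0.8^17 = 0.0225 < 0.025, so 17 of 17 rejects.
- For n = 17 to 25 every ACC patient must be AA-. From n = 26 one AA+ is allowed.

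**Step 2: the plan's own figure at a fixed count.** For n = 17 to 25 the power is 0.98^n:
- n = 18: 69.5%
- n = 19: 68.1%
- n = 20: 66.8%

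The stated figure of about 70% is reproduced as a rounded value near the expected count.

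**Step 3: the ACC count as a random number.** With N ~ Binomial(195, 0.10), the mean is 19.5 and the SD is √(195 × 0.10 × 0.90) = √17.55 = 4.19.

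| ACC count | Probability | Contribution to power |
|---|---|---|
| 16 or fewer | 24.2% | 0 |
| 17 to 25 | 67.8% | 44.9% |
| 26 or more | 8.0% | 7.2% |
| Total | 100% | 52.1% |

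The contribution is the sum over n of P(N = n) × power(n).

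**Step 4: other numbers assessed, 10% ACC.**

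| Assessed | Power | P(16 or fewer ACC) |
|---|---|---|
| 195 | 52.1% | 24.2% |
| 198 (= 220 × 0.9) | 53.7% | 22.1% |
| 220 (none incomplete) | 63.6% | 10.5% |

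**Step 5: other prevalences, 195 assessed.**

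| ACC prevalence | Power | P(16 or fewer ACC) |
|---|---|---|
| 8% (illustrative, not in the protocol) | 26.8% | 60.7% |
| 10% (section 8.3) | 52.1% | 24.2% |
| 12.5% (upper bound in section 8.2) | 71.8% | 3.9% |

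All these figures are for test 3 alone, before the requirement that tests 1 and 2 succeed first.

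**The case against.** **The figure is correct under its printed condition.** This stands. The count of about 20 is printed beside the power, and about 70% is a fair rounding at 18 to 20. A reader might infer a calculation error, and there is none. The fault is that a conditional figure serves as the power of a test whose sample size is random.

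**Test 1 was not demonstrably sized in another way.** A reader might infer that section 8.3 builds in room for a chance shortfall for test 1 but not for test 3. It says "For the exact test, at least 70 patients with a confirmed non-AA neoplasia are necessary", while 195 × 0.40 = 78 are expected. Averaging the exact power of test 1 over a random split also gives 79.6%, close to the stated 80%. But a fixed-count normal approximation for 90% against 98% gives 77.84, so 78 non-AA patients, and 78/0.40 = 195 exactly. The protocol does not say which route was used, so no inconsistency between the two tests can be claimed.

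**The minimum of 17 depends on the version of the exact test.** This stands in part. Section 8.2 prefers Blyth-Still-Casella to Clopper-Pearson for confidence intervals. If the test itself used such regions, 15 of 15 or 16 of 16 might count as significant, depending on the tie-break. With the favourable tie-break the averaged power at 195 is about 66%. Section 8.2 names that method for intervals and only where possible. For the test it names an exact binomial test.

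**A two-stage design could respond to a low ACC count.** Section 8.2 allows such designs where required, based on histology and blinded to the imaging result. It specifies none for test 3, so the stated power cannot rely on one.

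**The background prevalence might suggest almost no power.** Section 1.1 says that "adrenocortical carcinoma (ACC) is the most frequently observed adrenal malignancy with a prevalence of 4-6" percent. That concerns non-oncological patients with adrenal tumours in general, not the indeterminate masses selected here, so it does not contradict the 10% in section 8.3.

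**The consequence is limited.** This stands. Tests 3 and 4 did not drive the sample size and become exploratory if test 1 or 2 fails.

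**Conclusion.** The concern holds as a misstatement of unconditional power. Under the plan's own 195 assessed and 10% ACC, test 3 has about 52% power, some 18 points below the stated 70%, and about 24% of trials could not reach significance whatever the imaging shows. Even with all 220 assessable, power is about 64%. The stated level is reached at 195 assessed only if ACC prevalence is near the plan's upper bound of 12.5% (about 72%).

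These results assume the standard (Clopper-Pearson-type) exact test at 2.5% in the upper tail, a true value of 98%, and an ACC count that varies binomially. They do not depend on how 195 was derived. The protocol's sample size is not shown to be wrong.

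**What to change.** In section 8.3 and synopsis part E:
- Restate the power of test 3 as about 50% at 195 assessed patients with 10% ACC, and give 67–68% as the value conditional on 19–20 ACC patients being observed.
- Add that under the standard (Clopper-Pearson-type) exact test, significance is not attainable with fewer than 17 ACC patients.
- Preferably, add one sentence on the dependence on prevalence, for example about 72% at the 12.5% bound.

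The cost is a wording change in two places and a less favourable stated figure. No additional patients and no change to the test hierarchy are needed.

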### 8.4 Cost effectiveness analysis / Steroidobolomics

Economic analyses will be performed from a payer's perspective. Costs for diagnostic tests ( $[^{18}\text{F}]\text{FDG-PET}$ ,  $[^{123}\text{I}]\text{Iodometomidate}$ ), costs for non-surgical management and follow-up and costs for surgical procedures will be calculated according to the base rate of the University Hospital Würzburg and to the

national frequencies of relevant dose-related groups (DRGs). The incremental cost effectiveness ratio (ICER) per correctly assigned benign or malignant incidentaloma will be assessed for the individual imaging tests and the combination of both.

In addition to the investigations described above, all participants will be asked to collect a 24-h urine at baseline that will be subjected to steroid profiling by gas chromatography/mass spectrometry followed by machine-learning based computational analysis of results. This urine steroid metabolomics approach for differentiating benign from malignant adrenocortical tumors has been recently described (Arlt W et al., J Clin Endocrinol Metab 2011) and results will be compared accordingly with the results of Iodometomidate and FDG-PET prediction of malignancy.

## **8.5 Background and demographic characteristics**

Background and demographic characteristics as well as clinical characteristics will be analysed using standard descriptive techniques, e.g. tables of absolute and relative frequencies, means and standard deviations, median, quartiles, minimum and maximum.

## **8.6 Safety analysis**

Standard routine parameter changes from before imaging to prior to surgery will be assessed. Adverse events will be assessed from registration until end of follow up which is Visit 4. Surgery or biopsy of the adrenal lesion(s) is expected within the range of 1-6 weeks after the second imaging. Adverse and serious adverse events will be presented using standard descriptive statistical methods.

## **9 ADVERSE EVENTS AND SERIOUS ADVERSE EVENTS**

### **9.1 Definition**

#### **9.1.1 Adverse Event (AE)**

An Adverse Event (AE) is any new untoward medical occurrence or worsening of a pre-existing medical condition in a patient or clinical investigation subject administered an investigational (medicinal) product. An AE can therefore be any unfavourable and unintended sign (including abnormal laboratory findings for example), symptom, or disease temporally associated with the use of a medical product, whether or not a causal relationship (i.e. related/not related) with the treatment is suspected.

#### **9.1.2 Serious Adverse Event (SAE)**

A Serious Adverse Event (SAE) is any untoward medical occurrence that at any dose:

- is fatal (results in death)
- is life-threatening
- requires or prolongs in-patient hospitalization
- results in persistent or significant disability / incapacity
- is a congenital anomaly / birth defect
- is medically significant (defined as any clinical event or laboratory result that may not be immediately life-threatening or result in death or hospitalization but, based upon appropriate medical and scientific judgment, may jeopardize the subject or may require intervention (e.g. medical, surgical) to prevent one of the other serious outcomes listed in the definition above. Examples of such events include but are not limited to, allergic bronchospasm requiring intensive treatment in an emergency room or at home, blood dyscrasia or convulsions that do not result in inpatient hospitalization, development of drug dependency or drug abuse)

**A SAE judged as potentially related to a study drug qualifies as Serious Adverse Drug Reaction (SADR).**

**Events exclusively related to tumor relapse/progression or treatment of tumor relapse/progression are not considered SAEs.**

**NOTE:**

The following hospitalizations are **not** considered SAEs:

- A visit to the emergency room or other hospital department for less than 24 hours that does not result in admission (unless considered a “medically significant event” or a “life-threatening event”)
- Outpatient or same-day or ambulatory procedures
- Observation on short-stay units
- Hospitalization due to diagnostic procedures or standard supportive care (e.g. implant of central venous catheter, routine treatment or monitoring of the studied indication not associated with any deterioration in condition).
- The administration of blood or platelet transfusion as routine treatment of studied indication. However, hospitalization or prolonged hospitalization for a complication of such transfusion remains a reportable SAE.
- A pre-planned hospitalization for a condition which existed at the start of study drug and which did not worsen during the course of study drug treatment (e. g. scans, endoscopy, sampling for laboratory tests...). However, hospitalization or prolonged hospitalization for a complication of such procedures remains a reportable SAE.
- Social admission (e.g. subject has no place to sleep; hospice facilities)
- Administrative admission (e.g. for yearly physical examinations)
- Protocol-specified admission during a clinical trial (e.g. for a procedure required by the study protocol or for clinical research)
- Optional admission not associated with a precipitating clinical AE (e.g. for elective cosmetic surgery)

**9.2 Exposure to imaging during pregnancy/lactation**

In principle, pregnancy and lactation period are exclusion criteria. In the event of a pregnancy occurring during the course of the study, the subject must be withdrawn from the study immediately. The Safety Office unit must be notified within 24 hours if a pregnancy occurs during the study or within 30 days following the last administration of study treatment and the subject has to be followed during the entire course of pregnancy and postpartum period. Maternal and neonatal outcomes must be recorded even if they are completely normal and without AEs. The “Pregnancy report form” should be used.

## 9.3 Recording of adverse events

### 9.3.1 When to collect AEs

Any AE that occurs from the time consent is given to follow-up (V4) should be recorded.

All subjects should be monitored for AEs during the study. Assessments may include monitoring of any or all of the following parameters: the subject's clinical symptoms, laboratory, pathological, radiological or surgical findings, physical examination findings, or other appropriate tests and procedures.

